# Implementation and Effects of Information Technology-Based and Print-Based Interventions to Promote Physical Activity Among Community-Dwelling Older Adults: Protocol for a Randomized Crossover Trial

**DOI:** 10.2196/15168

**Published:** 2020-04-27

**Keywords:** physical activity, older adults, eHealth, print intervention, IT-based intervention, physical activity promotion, healthy aging, preferences, randomized trial

## Abstract

**Background:**

Despite the known health benefits of physical activity (PA), less than half and less than one-third of older adults in Germany reach the PA recommendations for endurance training and strength training, respectively, of the World Health Organization. The aim of this study is to investigate the implementation and effectiveness over the course of 9 months of two interventions (information technology [IT]-based vs print-based) for PA promotion among initially inactive older adults in a randomized, crossover trial. This study is part of a large research consortium (2015-2021) investigating different aspects of PA promotion. The IT-based intervention was previously developed and refined, while the print-based intervention was newly developed during this funding phase.

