**Methods:**

Our target sample size was 390 initially inactive community-dwelling older adults aged ≥60 years at baseline (3-month follow-up [T1]: expected n=300; 9-month follow-up [T2]: expected n=240) who were randomized to one of two interventions for self-monitoring PA: IT-based (50%) or print-based (50%) intervention. In addition, 30% of the IT-based intervention group received a PA tracker. At T1, participants in both groups could choose whether they prefered to keep their assigned intervention or cross over to the other group for the following 6 months (T2). Participants’ intervention preferences at baseline were collected retrospectively to run a post hoc matched-mismatched analysis. During the initial 3-month intervention period, both intervention groups were offered weekly group sessions that were continued monthly between T1 and T2. A self-administered questionnaire and 3D accelerometers were employed to assess changes in PA between baseline, T1, and T2. Adherence to PA recommendations, attendance at group sessions, and acceptance of the interventions were also tracked.

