Therefore, the main aim of this study was to compare the effects of 2 interventions using different modalities (IT-based vs print-based) among initially inactive older adults aged at least 60 years living in 14 community districts in 2 geographically different regions (northwest and northeast) of the city of Bremen, Germany. Further, participants’ preferences regarding the intervention modality were addressed by conducting a randomized trial with a crossover design. At baseline, participants were randomized to either a 10-week IT-based or print-based intervention. A random subsample of the IT-based intervention group (30%) also received a PA tracker. After the 3-month follow-up, participants could choose whether they wanted to remain in the same intervention group and keep their assigned material or switch to the other group for the following 6 months. They could also choose to use a PA tracker at this stage.

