### Study Aims

Hence, based on previous findings of the literature and knowledge gained during the preceding trial, this study aimed to adapt and simplify the IT-based intervention of the first funding phase further to improve usability and develop a simple print-based intervention that initially inactive participants with little affinity to technology find easy to interact with; investigate the implementation, feasibility, and use of 2 interventions (IT-based vs print-based) as well as changes in PA among older adults (aged ≥60 years) in a randomized trial with a crossover design over the course of 9 months; examine the role of personal preferences for different delivery modes with regard to intervention effectiveness; and explore associations between changes in PA and possible changes in physical fitness and cognitive capacity in a pooled sample of participants from both phases of funding.

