### Study Design

After determination of eligibility, study participants were randomized to either an IT-based intervention or a print-based intervention (see Figure 1). In the first group, 30% were randomly selected to receive a PA tracker in addition to access to the website. Weekly time slots were randomly assigned to both intervention groups. Then, we had participants choose appointments according to their personal time constraints without knowing which intervention group they were assigned to. All intervention groups were offered weekly group sessions, and participants were encouraged to attend each of them. Two weeks before the intervention started, participants in all groups attended an introductory event where they were informed about the study background and procedures. On this day, data collection also started, and participants received the activity tracker and questionnaires for the first time (T0). They were also briefed about their randomization to one of the intervention groups and the existence of the other groups. Therefore, they were not blinded. Participants were given the choice to remain in their intervention group or to cross over to the other group after 3 months (and a 10-week intervention period). With that, a crossover design with the following possible combinations was generated: IT-IT, print-print (matched), or IT-print and print-IT. Preferences regarding the intervention material assessed retrospectively at the 9-month follow-up will be taken into account when analyzing intervention effects later in the study. Research staff members conducting the study were not blinded, and the statistician will not be blinded when analyzing the data.

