### Analytic Strategy

Effects of time and group (main outcomes: subjective and objective measures of PA) will be examined in multivariate analyses. In addition, covariates, such as gender, age, and preferences regarding intervention material, and individual contextual factors (eg, living or social environment) will be taken into account. Furthermore, we will analyze how the intervention enables study participants to change their behavior by running mediation analyses. The estimated target sample size of 390 participants for this study is based on the results of 2 recently published studies on PA in adults [27,28] that reported a mean 111 weekly minutes (SD 116.8 weekly minutes) of MVPA and an intervention effect of an increase in MVPA of 77 minutes per week. However, in a conservative (or realistic) approach, we assumed that the mean increase in MVPA in our study will reach only 40 minutes/week. To detect such a difference between the intervention and control groups with a power of 80% at an alpha of .05 (two-sided), a net sample size of 150 subjects for each group is required. Assuming a loss to follow-up from T0 to T1 of 20-25% (ie, ca. 23%), it is necessary to initially recruit 390 study participants (ie, 195 per group at baseline). Assuming another 20% loss to follow-up from T1 to T2, we expect that approximately 240 individuals at T2 will self-select to one of the 4 groups: IT-IT, print-print, IT-print, or print-IT. Should participants self-select equally into each group (n=60), we will still be able to detect the mean difference of 77 minutes/week [28] between each group, by means of an appropriate post hoc test that is adjusted for multiple comparisons.

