**Figure 2 figure2:**
[figure not shown]
Weekly overview of physical activity performed, as provided to participants in the IT-based intervention group.

Paralleling the 10-week IT-based and print-based interventions, weekly group sessions with up to 25 participants per group were offered separately to both intervention groups. Trained student assistants led these sessions in which participants performed endurance, strength, balance, and flexibility exercises in groups or went for walks in the communities. Each session was 90 minutes long and designed to include 60 minutes of exercise, 10 minutes of answering questions, and 20 minutes of discussion of topics surrounding healthy aging that changed every week (eg, social support, relaxation, pain management). During their first weekly group meeting, participants received the necessary equipment (printed material or information to access the website and/or a Fitbit) and a comprehensive introduction on how to use the equipment and materials. After the first follow-up, interventions continued for another 6 months. After the initial 10 weeks of the interventions, the weekly group meetings were replaced with monthly events held over the course of the following 6 months. During these events, participants of all intervention groups were offered workshops and lectures on lifestyle-related topics, such as healthy nutrition in older age, overcoming loneliness, and strategies for developing healthy habits.

We will develop a toolbox during this project that will include both IT-based and print-based interventions and all related intervention materials that can be used later for long-term implementation and dissemination via different stakeholder groups (for further detail, please see the Discussion).

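### Beyond month 3, randomisation does not identify the 9-month IT-versus-print aim, because every participant then chooses the mode

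*Protocol article*

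**What the plan says.** **Aim.** The abstract's Background sets out to study "effectiveness over the course of 9 months of two interventions (information technology [IT]-based vs print-based) for PA promotion among initially inactive older adults". The Study Aims section speaks of "changes in PA among older adults (aged ≥60 years) in a randomized trial with a crossover design over the course of 9 months". The Discussion promises answers on whether IT or print helps people both take up and keep up regular activity.

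**Allocation.** The abstract's Methods give the randomised split as "IT-based (50%) or print-based (50%) intervention".

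**What happens at T1.** Study Design states: "Participants were given the choice to remain in their intervention group or to cross over to the other group after 3 months". The last paragraph of the Introduction adds, about the tracker: "They could also choose to use a PA tracker at this stage". Study Design concludes that "a crossover design with the following possible combinations was generated" and lists IT-IT, print-print, IT-print and print-IT.

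**How T2 is sized.** The Analytic Strategy expects about 240 people at T2 in those four groups. It makes a power statement for a difference of 77 min/week between groups, introduced by "Should participants self-select equally into each group (n=60".

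**Limitations.** The Discussion names three: no control group, a target population that is hard to recruit, and possible recall bias in the retrospective preference item. Self-selected mode after T1 is not among them.

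**The concern.** An effectiveness claim for IT against print over 9 months needs two groups that differ in mode by chance over those 9 months. Here chance governs the first 3 months and the participant governs the other 6. Two T2 comparisons are then available, and neither answers the stated aim:

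- **By randomised arm.** This is protected by randomisation, but it compares two starting modes, each followed by free choice.
- **By pathway.** This comes closer to sustained IT against sustained print, but the pathways are formed by a choice made after three months' experience of the intervention. People who stay and people who switch may differ in motivation, early success or ease with technology.

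At stake is how a T2 result is read. A small difference between arms could be taken as equal long-term effectiveness when switching may have diluted it. A pathway difference could be credited to mode when it reflects who chose what. The words randomised and crossover in the title and abstract encourage both readings.

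**Working it through.** **Inputs, all from the Analytic Strategy:** net 150 per group at T1; loss of about 23% from T0 to T1; a further 20% loss from T1 to T2; planning difference 40 min/week; 60 per pathway, conditional on an equal split.

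**Step 1. Reproduce the article's T2 numbers.**

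- 150 / (1 − 0.23) = 194.8, so 195 per arm and 390 in total.
- 300 × (1 − 0.20) = 240 at T2.
- 240 / 4 = 60 per pathway.

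These agree with the article.

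**Step 2. Mode mix in months 3 to 9.** Let s1 be the share of the IT arm that moves to print, and s2 the share of the print arm that moves to IT. After T1 the share using IT is 1 − s1 in the IT arm and s2 in the print arm. The arms therefore differ in current mode by

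c = 1 − s1 − s2.

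In the equal-split scenario each arm has 120 people, 60 of whom switch, so s1 = s2 = 60/120 = 0.5 and c = 0. Over the whole 9 months the average difference in mode is then (3 × 1 + 6 × 0)/9 = 0.33, all of it from the first 3 months.

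**Step 3. Effect on the T2 difference.** The article gives no switching rate, so a range is shown. Assumptions: the effect at T2 follows the mode in use, nothing carries over from the first 3 months, and both arms switch equally (s1 = s2 = s). The expected difference by arm is then 40 × (1 − 2s).

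| Switching in each arm | Retained mode contrast | Expected T2 difference by arm (min/week) |
|---|---|---|
| 0% | 1.0 | 40 |
| 10% | 0.8 | 32 |
| 25% | 0.5 | 20 |
| 50% | 0 | 0 |

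**Step 4. What changes if the starting mode leaves a lasting effect.** Write D for the effect of current mode and C for any effect of starting mode that persists to T2. In this simple form the arms differ by D × c + C. With c = 0 the comparison carries no information on D, yet it need not be zero, because C may not be. At any other c, one observed difference cannot separate D from C. This is why the problem is one of identification and not only of dilution.

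**The case against.** **The design is open about the choice.** The option to switch is stated in the abstract, Introduction, Study Design and Analytic Strategy, and the Discussion calls the design preference-based. That is true of the procedure. Its consequence for the 9-month aim is not stated, and the limitations omit it.

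**The aim is read at its strongest.** The abstract's Objective and the main aim in the Introduction give no 9-month horizon. The Study Aims speak of implementation, use and changes in activity, and the Results predict no IT-print difference at T2. This lowers the weight of the point. The abstract's Background still makes the 9-month effectiveness claim, and the Discussion's reference to keeping up activity echoes it.

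**An analysis plan could deal with it.** Adjusted pathway analyses can be specified, but they rest on having measured why people switched. No model supplies a randomised mode contrast that the design does not create.

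A reader might also infer more than the documents support:

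- *That there is no randomised comparison at all.* Months 0 to 3 are a randomised IT-versus-print comparison, and the arms as randomised can still be compared at T2.
- *That half of each arm is expected to switch.* The 60 per pathway is a conditional illustration for a power statement. No switching rate is forecast.
- *That the T2 difference must vanish.* That needs balancing switching, such as 50% in each arm, and no carry-over. Both interventions teach self-monitoring, so an effect of starting mode could persist.
- *That a stated power figure is wrong.* The article sizes T2 for four pathways at 77 min/week and makes no power statement for a two-arm T2 test.
- *That within-person IT-print contrasts will be confounded with period.* None is proposed. The change in group format, where "the weekly group meetings were replaced with monthly events held over the course of the following 6 months", applies to both arms.

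**Conclusion.** The point holds in limited form. The IT-versus-print effectiveness aim is identified by randomisation up to T1 and not beyond it. At T2 the arms as randomised estimate the effect of the starting mode followed by free choice, and the four pathways are observational groups. This follows from the article's description of the design and needs no numerical assumption.

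The size is uncertain. Equal switching of 10% to 50% would reduce a 40 min/week difference to between 32 and 0 min/week. That range assumes the effect follows the mode in use, with no carry-over and the same switching in both arms; the article states none of these. The zero contrast in mode belongs only to switching that balances between the arms, of which the equal split is one case.

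The wording should be corrected, because it changes what the trial may conclude at 9 months. The 3-month comparison is unaffected.

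**What to change.** 1. In the aims, abstract and conclusions, limit the randomised claim about IT-versus-print effectiveness to T1.
2. Define the T2 comparison by randomised arm as the effect of the starting mode followed by free choice. Report beside it the share of each arm using each mode, and the tracker, in months 3 to 9.
3. Label all comparisons among the four pathways as non-randomised, including the pairwise tests for which the Analytic Strategy gives power.
4. Describe the design as a randomised parallel-group trial with an optional switch at 3 months.
5. Add self-selected mode after T1 to the limitations in the Discussion.

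The cost is a narrower 9-month claim and some redrafting. No new data are needed: the pathways already record who stayed and who switched.

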**Objective:**

We aim to compare the effectiveness and examine the preferences of study participants regarding both delivery modes.

**Methods:**

Our target sample size was 390 initially inactive community-dwelling older adults aged ≥60 years at baseline (3-month follow-up [T1]: expected n=300; 9-month follow-up [T2]: expected n=240) who were randomized to one of two interventions for self-monitoring PA: IT-based (50%) or print-based (50%) intervention. In addition, 30% of the IT-based intervention group received a PA tracker. At T1, participants in both groups could choose whether they prefered to keep their assigned intervention or cross over to the other group for the following 6 months (T2). Participants’ intervention preferences at baseline were collected retrospectively to run a post hoc matched-mismatched analysis. During the initial 3-month intervention period, both intervention groups were offered weekly group sessions that were continued monthly between T1 and T2. A self-administered questionnaire and 3D accelerometers were employed to assess changes in PA between baseline, T1, and T2. Adherence to PA recommendations, attendance at group sessions, and acceptance of the interventions were also tracked.

**Results:**

The funding period started in February 2018 and ends in January 2021. We obtained institutional review board approval for the study from the Medical Association in Bremen on July 3, 2018. Data collection was completed on January 31, 2020, and data cleaning and analysis started in February 2020. We expect to publish the first results by the end of the funding period.

**Conclusions:**

Strategies to promote active aging are of particular relevance in Germany, as 29% of the population is projected to be ≥65 years old by 2030. Regular PA is a key contributor to healthy aging. This study will provide insights into the acceptance and effectiveness of IT-based vs print-based interventions to promote PA in initially inactive individuals aged ≥60 years. Results obtained in this study will improve the existing evidence base on the effectiveness of community-based PA interventions in Germany and will inform efforts to anchor evidence-based PA interventions in community structures and organizations via an allocation of permanent health insurance funds.

**Trial Registration:**

German Registry of Clinical Trials DRKS00016073; https://tinyurl.com/y983586m

**International Registered Report Identifier (IRRID):**

DERR1-10.2196/15168

## Introduction

In Germany, approximately 91% of all deaths are attributable to noncommunicable diseases [1]. Physical inactivity is the fourth leading risk factor contributing to the development of noncommunicable diseases and overall mortality [2]. Conversely, regular physical activity (PA) and the reduction of an inactive lifestyle [3] are associated with improvements in physical, cognitive, and functional health over the lifespan [3,4].

The World Health Organization (WHO) and American College of Sports Medicine recommend that adults aged 18 to 64 years, as well as those 65 years and older, should perform moderate-to-vigorous endurance training for at least 150 minutes per week (in bouts of at least 10 minutes) [2]. In addition, adults aged 65 years and older should perform flexibility, strength, and balance training twice per week [5,6]. Furthermore, Rütten and Pfeiffer [7] state in the German national recommendations for PA that adults should generally avoid extended periods of sitting and, where possible, take PA breaks from sitting. According to the authors, “a major health benefit of PA can already be observed when persons who were entirely physically inactive start becoming active to a small extent meaning that every increase in PA is associated with a health benefit. Every single step away from sedentary behavior is important and promotes health” [7].

In Germany, only 42% of adults aged 65 years and older currently meet the recommendations for endurance (at least 150 minutes per week of moderate activity, at least 75 minutes of intense activity, or a combination of both, in bouts of at least 10 minutes), and 29% meet the recommendations for strength training [6], indicating a need for interventions for PA promotion targeting the general population of older adults. An earlier survey spanning the years 2008 to 2011 reported that merely 18% of German adults aged 60 to 69 years and 14% of adults aged 70 to 79 years exercised moderately to vigorously for at least 150 minutes per week [8]. To tackle this public health issue in Germany and facilitate PA promotion, the Federal Ministry of Health recommends the development and implementation of population-based informational intervention approaches or campaigns, community-based interventions, and policy and environmental approaches for PA promotion [7]. According to the current state of research, results of several reviews suggest that interventions for PA promotion, including mass media campaigns, motivational decision aids, community-based multicomponent interventions, and environmental approaches, can effectively increase PA in the general population [7]. Evidence regarding the benefit of using theory during intervention development to achieve greater impact on behavior change is still contradictory [9]. On the one hand, there is some evidence suggesting that interventions based on behavior change techniques rooted in theory are effective in altering behavior [9]. On the other hand, results of one meta-analysis indicate that a theoretical basis leads to no difference in intervention effectiveness [10], maybe also due to the fact that the behavior preferences of study participants were not sufficiently taken into account [11]. Theories and theoretical assumptions about mechanisms, processes, and techniques are needed to better understand individuals and their needs and to avoid always reinventing the wheel when developing interventions but rather building on previous evidence [3,9,10].

Multiple studies have investigated the role of different modalities of delivering these interventions to older adults. Evidence suggests that participation in interventions providing information on PA either in a face-to-face setting or as print versions leads to increased PA levels in older adults [12-14]. Information technology (IT)-based PA interventions have the advantage of potentially reaching a large number of people in a cost-effective manner [15]. In addition, intervention material can be easily accessed, and instantaneous feedback on behavior change can be provided [10,15]. They also appear to have a positive impact on PA [3,16]. Results of a systematic review comparing the effectiveness of electronic health (eHealth) interventions promoting PA in older adults aged 55 years and older with either no intervention or a non-eHealth intervention indicate that eHealth interventions can effectively promote PA in this population in the short-term, while evidence regarding long-term effects is still lacking [3,9,17]. The results of this review are inconclusive regarding the question of whether eHealth interventions have a greater impact on PA behavior among older adults than non-eHealth (eg, print-based) interventions [17]. Also, the effects of combining various eHealth intervention components are still unclear.

Two studies investigated the added benefit of using Fitbit activity trackers in addition to a website to monitor PA on total weekly PA levels and moderate-to-vigorous PA (MVPA) [18,19]. In a sample of overweight adults, Vandelanotte et al [18] demonstrated a significant increase in total weekly PA and MVPA after 3 months for a group of participants using a Fitbit compared with a group of participants not using a Fitbit. Although sitting time decreased over time, this effect was not significant [18]. With a sample of older adults, Muellmann et al [19] found no significant differences in PA levels between a group using a Fitbit compared with a group not using a Fitbit. However, participants in the Fitbit group had slightly greater increases in MVPA and decreases in sedentary time than participants in the non-Fitbit group after 3 months [19]. While more participants in the non-Fitbit group did not complete the follow-up after 3 months than in the Fitbit group (63% vs 36%) in the first study [18], the reverse was true in the second study [19]. More participants in the Fitbit group did not complete the 3-month follow-up than in the non-Fitbit group (40% vs 31%) [19]. It is conceivable that individual preferences for interventions may have influenced dropout and possibly adherence to the interventions [10,11,13]. Participants may have been randomized to an intervention that they would not have picked had they been given a choice and that they may have found difficult to interact with.

The effects of study participants’ preferences on treatment or intervention outcomes in randomized controlled trials are still not well understood [20,21]. There is some indication that the preferences for delivery mode vary by the sociodemographic characteristics of participants, such as age, gender, and living environment, or by weight status [13,22]. For example, preference for an IT-based intervention was positively related with being 35 years or older (compared to younger ages) and high levels of internet use and was negatively associated with female gender. Preference for a print-based intervention was associated with older age and negatively associated with female gender and obesity [22]. Further, evidence suggests that sociodemographic variables may explain variations in the use of PA trackers [23] and that use of trackers in PA interventions should be aligned with preferences of different target groups [13].

Therefore, the main aim of this study was to compare the effects of 2 interventions using different modalities (IT-based vs print-based) among initially inactive older adults aged at least 60 years living in 14 community districts in 2 geographically different regions (northwest and northeast) of the city of Bremen, Germany. Further, participants’ preferences regarding the intervention modality were addressed by conducting a randomized trial with a crossover design. At baseline, participants were randomized to either a 10-week IT-based or print-based intervention. A random subsample of the IT-based intervention group (30%) also received a PA tracker. After the 3-month follow-up, participants could choose whether they wanted to remain in the same intervention group and keep their assigned material or switch to the other group for the following 6 months. They could also choose to use a PA tracker at this stage.

